## Community Mobilization

The objective of the study’s community mobilization strategy is to both communicate the purpose and nature of the proposed study to the community, and to also solicit community input on study activities on an ongoing basis. The following community groups are the primary target groups for this study’s mobilization activities:

1. Community Advisory Group
2. Provincial administration
3. Ministry of Health (County, Sub-County, individual clinics)
4. Local NGOs
5. Community Health units (Community Health Extension Workers, Community Health Workers)
6. Churches
7. Beach Management Unit
8. Communities within the study area

Beginning several months before commencement of participant recruitment, study staff will meet with representatives of each of the above groups in the communities included in the study to explain the nature of the study and solicit feedback. The study will also form a Community Advisory Group composed of community representatives. This group will meet monthly to hear updates on study progress and provide ongoing feedback from the community. After meeting with representatives from the above groups, mobilization will procede to community-wide mobilization. Chief’s barazas will be held in each sub-location included in the study to communicate the nature of the study to the community at large.

Given the nature of study recruitment and the phased roll-out of the study a carefully crafted message will be presented to the community regarding the way that microclinic groups are formed. Community members will be informed that we are expanding the microclinic program to all parts of Mfangano, Remba and Ringiti islands. To facilitate this expansion, we are starting with a small number of groups in the first phase in order to study how the program works at this larger scale. After completion of phase 1, those who were not able to join the program initially will then have an opportunity to join. This approach will allow for cover from stigma regarding the way that groups are initially formed, and will also help both control group index participants and other community members not feel left out of the program.

Following completion of the study and during the second phase of expansion where open microclinic enrollment is allowed (and where control group members will receive the intervention), study results will also be communicated back to participating communities. Chief’s barazas will be held to communicate findings back to the community at-large. Individual meetings with the above groups will also be held to further facilitate report-back of results.

## Procedures

### Study Design Overview

This is an individual randomized control trial evaluating the impact of the social network-based microclinic intervention on engagement and retention in HIV care over twelve months of follow up among individuals who have missed a clinic appointment by >3 days.

Study enrollment will occur over a six-month period. Upon meeting eligibility criteria, study staff will trace participants in the community to enroll them in the study. Eligibility will be determined using an Eligibility Determination Form, adapted from the FACES Loss to Follow-Up form (Appendix A). Study staff will counsel all eligible participants to return to clinic. After this counseling session, study staff will explain the purpose of the study and the nature of the intervention. After answering all participant questions, interested participants will be consented to participate (Section IX.c and Appendix H). Following study enrollment, participants will be randomized to intervention or control arm. Those randomized to intervention will be invited to recruit their social network members to form a microclinic. Study staff will provide confidential assistance to help discreetly identify and recruit family, friends, and neighbors to join the program based on previous protocols developed during the Mfangano Health Net Microclinic Pilot Program. Participants randomized to the control arm will be invited to form a microclinic group after the conclusion of the study.

Baseline measurements for index participants (i.e. participants who are eligible based on missed clinic visit) will be taken at study enrollment, with study staff administering a survey to collect data on baseline participant characteristics (Appendix C). Reasons for initial disengagement from care will also be recorded.

The microclinic intervention includes participation by members of the index patient’s social network. This may include other index patients, or community members who are HIV-infected, HIV-uninfected or of unknown HIV status. These non-index microclinic members, referred to as ‘social network’ participants, will be invited to join the study in addition to participation in a microclinic group. Microclinic participant is not contingent on study participation, however data will only be collected for microclinic group members who also consent to study participation.(Appendix I) For social network participants, study participation involves completion of a baseline survey to collect information on sociodemographic characteristics, HIV-related stigma, previous HIV testing, HIV status, and enrollment and engagement in HIV care (if HIV-infected).(Appendix D) For each microclinic group, a Microclinic Group Member Information form will also be completed to describe the nature of the realtionships between group members.(Appendix E) Only group members who consented to study participation will be included. At the time of group enrollment, all prospective social network study participants will be invited to enroll in the study. Following study enrollment, these surveys to collect information on sociodemographic characteristics and HIV-related stigma will be administered by trained study staff. Data on previous HIV testing, HIV status and enrollment and engagement in HIV care will be collected by a trained Voluntary Counseling and Testing (VCT) counselor as part of a baseline HIV counseling and testing session. Refusal to participate in the study will not preclude social network group members from participating in the microclinic group, but no study data will be collected on these participants.

A full clinic visit history will be obtained for all study participants on HIV care and treatment at any of the included study sites. Visit history data will be obtained from the FACES-MOH “Blue Cards”. For patients who made an official tranfer to another facilities within Nyanza Province, study staff will visit that facility to confirm the transfer and obtain a complete clinic visit history following the transfer. In addition to data on clinic visit attendance, patient enrollment date, ART initiation date, ART regimen, CD4 measurements, viral load measurements, pharmacy pick up, vital status and locator information will also be collected. All participants lost to follow-up from clinical care during the course of the study will be traced to ascertain vital and clinical status (i.e. disengagement from any clinical care, transfer to another facility, death while ‘in care’ or death after disengaging from care). For patients who made an unofficial transfer to another health facility in Nyanza Province, study staff will visit that facility to obtain visit history as was described for the official transfers. For patients who are disengaged from clinical care at the time of tracing, barriers to return to care will be identified and participants will be counseled to return to care. Clinic staff will be informed of any additional information gained in the field regarding the vital or clinical status of patients who were lost to follow up from clinical care.

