### Measurements

The predictor of interest is the baseline treatment assignment, as determined by randomization. All analysis will be conducted using an intention-to-treat analysis.

Covariates of interest will be collected through participant surveys at baseline and study closure, as well as routine clinic data collected at the participant’s original clinic and any other clinics from which he or she receives HIV care during the course of the study. Baseline surveys (Appendix C) will collect data related to the following:

1. Demographic characteristics
2. Contact and locator information
3. HIV-related stigma[23](#_ENREF_23)
4. HIV status disclosure
5. Social support
6. Clinic data (date first HIV positive, date of enrollment)
7. Reason for missed clinic appointment, including name of other facilities where care was received

At the end-of-study survey (Appendix G), additional data will be collected related to possible adverse events that may or may not be related to the intervention. In addition to specific questions in the survey, an open-ended question will be used to assess other adverse experiences related to issues such as stigma, unintended disclosure or poor treatment by health center staff. Participants will be asked whether they attribute any or all of these experiences to participation in the study. Additionally, participants in the intervention arm will specifically be asked about adverse experiences related to group status disclosure, again using both a checklist and an open-ended question. At the end-of-study survey, patients will be asked if they are currently in care and, if so, which clinic. Reasons for transfer or disengagement from the original clinic will be assessed. For patients who were lost-to-follow-up (missed a clinic visit by ≥90 days and did not return to clinic) or who transferred out from their original clinic, a patient tracing survey will also be conducted. (Appendix F) See description of clinic data capture below regarding determination of patient’s visit history and transfer status.

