In addition to survey data, clinical data will also be collected for all study participants. Chart review will be conducted at participant’s clinic of origin to collect data on baseline disease status, and clinical and laboratory data over the course of the study (CD4 count, WHO stage, viral load). Other clinical data will include date of first HIV test, date of clinic enrollment, date of ART initiation (if applicable), complete visit history, patient tracing visits conducted by clinic staff, patient death and patient transfer. For patients who transfer to other sites, study staff will visit that site to confirm that transfer occurred and obtain the above clinic data available for the patient after the transfer (either through physical chart review or the OpenMRS electronic medical record). Data obtained from clinics will be limited to data that was collected during routine patient care.

Qualitative Data Collection

Focus Group Discussions:

Twelve (12) focus group discussions will be conducted at the conclusion of the intervention phase of the study. It will be reiterated to all participants that focus group participation is completely voluntary and that refusal to participate as well as any issues discussed within the focus group will have no effect whatsoever on relationships with FACES and OHR. All FG participants will complete a separate Qualitative Consent Form (Appendix K). Each Focus group will follow the discussion protocol outlined in Appendix L – Focus Group Discussion Guide.

- - - Eight (8) focus group discussions with study participants (5-15 people each). A convienience sample of participants will be identified and selected by research staff during enrollment, and follow-up, based on availability and interest in participating in Focus Group discussions.
    - Two (2) focus group discussions with CHW Facilitators who lead and conduct the micro-clinic training program.
    - Two (2) focus group discussions with the FACES/OHR staff implementing the Microclinic intervention.

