Because all eligible study participants will have recently missed an appointment, we are interested in the rate of reconnection to care. Reconection to care will be defined as return to any HIV clinic and receiving a refill of that patient’s ART or co-trimoxazole prophylaxis. We will depict time to reconnection to care by study arm using the Cumulative Incidence function, with death as a competing event.[24](#_ENREF_24) We will formally test the differece in the rate of reconnection to care using a Cox proportional hazards model. Standard errors will be adjusted for clustering, as in Hypothesis 1. Validity of the proportional hazards assumption will be assessed graphically and through formal testing using Schoenfeld residuals.

Hypothesis 4

The proportion of paritipcants alive and retained in care at the end of 12 months of follow-up will be compared between study arms using simple chi-squared analysis. Retention is defined as being alive and not missing a clinic appointment by 90 days or more as of study closure at 12 months post- study enrollment.

Hypothesis 5

The proportion of participants who are alive and virally suppressed at the end of the study will be compared between study arms using chi-squared testing. Viral load testing conducted within 180 days of the 12-month timepoint post study enrollment will be used for analysis. As above, viral loads utilized for analysis will be collected during routine patient care. Primary analysis will be conducted on an intention to treat basis, with missing values assumed to be virologically non-suppressed. Sensitivity analysis will be conducted using completer analysis, where only participants with measured viral loads will be included. In this sensitivity analysis, participants who died or who disengaged from care will be included as virologically non-suppressed.

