|  ***Questions C5k is only for deceased patients not yet started on ART at original clinic.*** | | | | | | | | | | | | | | | | | | |
|  C5k. Had he/she started ART somewhere else besides [name of original clinic]? | |  Yes   No**Go to Section E**   Not asked **Go to Section E**   Unknown**Go to Section E** | | C5k(i). When did he/she start ART? | | | | | | - -  DAY(*dd*) MONTH (mmm) YEAR **(yy)** | | | | | | | |  Unknown |

| **SECTION D: TRACKER UNABLE TO COMMUNICATE WITH PATIENT OR INFORMANT** Check local death registry: | | | | | | | |
| --- | --- | --- | --- | --- | --- | --- | --- |
| D1. Is the patient dead? | |  Yes   No evidence of death in registry  (registry consulted)   Unknown (no registry data  available) | |  D1a. When did the patient die? | | | - -  DAY(*dd*) MONTH (mmm) YEAR **(yy)** |
| ** GO TO SECTION E** | | | | | | | |
| **SECTION E: TRANSFER CLINIC DATA** | | | | | | | |
| F1. Did participant receive care from another health care facility at any time during the study? | | | | | | | |
|  Yes,  *list names and date of first attendance* | F1a. Facility name | |  | | F1b. Date first received services | - -  DAY(*dd*) MONTH (mmm) YEAR **(yy)** | |
| F1c. Facility name | |  | | F1d. Date first received services | - -  DAY(*dd*) MONTH (mmm) YEAR **(yy)** | |
| F1e. Facility name | |  | | F1f. Date first received services | - -  DAY(*dd*) MONTH (mmm) YEAR **(yy)** | |
| ** Collect visit history from transfer clinics using VISIT HISTORY FORM** | | | | | | |
|  No | ** END** | | | | | | |

| **SECTION F: TRACKER FEEDBACK** | | | | | | | | | |
| --- | --- | --- | --- | --- | --- | --- | --- | --- | --- |
| F1. How many persons were questioned by phone or in person while looking for this patient? | | | | |  |  | | --- | --- | | | F2. How many hours were spent by phone or in person looking for this patient? | | : | |
| Hours *(hh)* : Minutes *(mm*) | |
| F2b. How many trips were made looking for this patient? | | | |  |  | | --- | --- | |  Not applicable, phone tracking only | | | | | |
| F3. Does patient have a new site or residence? | | |  Yes: Address known  *Update contact form*   Yes: He/she has moved but do not know where   No   Don’t Know  Not applicable (died) | | | | F4. Does the patient have a new phone contact number? | |  Yes: *Update contact form*   No   Don’t Know   Not applicable (died) |

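### The protocol limits post-transfer visit histories to Nyanza Province in one section and sets no limit in others, so continued care elsewhere may be scored as time out of care or absence in both primary outcomes

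*Protocol*

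**What the plan says.** Section VIII.F of the protocol, Study Design Overview, sets out how visit histories are obtained after a transfer. For official transfers: "For patients who made an official tranfer to another facilities within Nyanza Province, study staff will visit that facility to confirm the transfer". For unofficial ones: "For patients who made an unofficial transfer to another health facility in Nyanza Province, study staff will visit that facility to obtain visit history". Both sentences carry the provincial limit. The same paragraph has everyone lost from clinical care traced, with transfer to another facility classed separately from disengagement.

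The Measurements subsection of VIII.F covers the same task without a limit: "For patients who transfer to other sites, study staff will visit that site to confirm that transfer occurred and obtain the above clinic data". It allows two sources, "either through physical chart review or the OpenMRS electronic medical record". Appendix F, the tracing form, lists every other facility attended and the date of first attendance, wherever the facility is, and then instructs: "Collect visit history from transfer clinics using VISIT HISTORY FORM".

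Section VIII.G builds the outcomes on these data. Hypothesis 1 compares 90-day absence in a Cox model, and death is the only competing event named for the cumulative incidence curve. Hypothesis 2 counts days out of care from each missed appointment to the next clinic visit. Hypothesis 3 treats care as care anywhere: "Reconection to care will be defined as return to any HIV clinic".

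**The concern.** The two rules tell field staff different things about a participant who moves beyond Nyanza and attends a clinic there. Under the Study Design Overview no history is sought from that clinic. Under Measurements and Appendix F it is.

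If the narrower rule is followed, the study file for that person stops at the transfer. Tracing may establish that the person transferred, but the Hypothesis 2 calculation needs a next clinic visit and there is none on file. On its natural reading, days out of care then accumulate until follow-up ends. A missed appointment at the clinic of origin with no later visit recorded also looks like a 90-day absence under Hypothesis 1.

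The trial sets out to measure engagement in HIV care, and its own tracing categories separate transfer from disengagement. Scoring care elsewhere as absence would therefore measure the wrong thing in both primary outcomes. The choice has to be settled before data collection, because no later analysis can recover histories that were never collected.

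**Working it through.** **Scope, section by section**

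| Place in protocol | Post-transfer histories sought from |
|---|---|
| VIII.F Study Design Overview, official transfers | Nyanza Province |
| VIII.F Study Design Overview, unofficial transfers | Nyanza Province |
| VIII.F Measurements | other sites, no limit |
| Appendix F, transfer clinic data | transfer clinics, no limit |

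**The plan's sample size.** Inputs from VIII.C Sampling: event rates p1 = 0.25 and p2 = 0.125, alpha 0.05 (two-sided assumed), power 0.80, m = 2 participants per group, coefficient of variation k = 0.25. The Hayes-Bennett formula for clusters per arm is

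c = 1 + (z_a + z_b)² × V / (p1 − p2)², with V = p1(1 − p1)/m + p2(1 − p2)/m + k²(p1² + p2²).

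Here V = 0.1533 and (z_a + z_b)² = 7.849, so c = 1 + 7.849 × 0.1533 / 0.015625 = 78.02. Two per cluster gives 156 per arm, as stated. Attrition: 156/0.9 = 173.3, or 174, against the stated 175, which is close enough.

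**What misclassification would do.** The documents give no rate of transfer out of the province. Assume that a share x of otherwise event-free participants in each arm stays in care elsewhere and is scored absent:

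- control risk a = 0.25 + 0.75x
- intervention risk b = 0.125 + 0.875x
- power = Φ[(a − b)/√(V/(c − 1)) − 1.96], with V recalculated at a and b, and c = n/2
- hazard ratio = ln(1 − b)/ln(1 − a)

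| x | control | intervention | HR | power, 156 per arm | power, 175 to 180 per arm |
|---|---|---|---|---|---|
| 0 | 0.250 | 0.125 | 0.46 | 80.0% | 84 to 85% |
| 1.4% | 0.261 | 0.137 | 0.49 | 76.9% | 82 to 83% |
| 3% | 0.273 | 0.151 | 0.52 | 73.4% | 78 to 79% |
| 5% | 0.288 | 0.169 | 0.55 | 69.1% | 74 to 75% |

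The 1.4% is the complement of the 98.6% outcome ascertainment in the pilot study (100 − 98.6). It is used only as a scale, since those participants were not shown to be transfers. The last column assumes no other attrition.

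**Unequal shares, 156 per arm**

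- 2% control, 5% intervention: 0.265 vs 0.169, risk ratio 0.64, power 53%.
- 5% control, 2% intervention: 0.288 vs 0.143, risk ratio 0.50, power 87%.

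**If such participants are not scored absent.** Take the worst case, in which they are dropped entirely and n falls to 156(1 − x). Power is then 77.9% at x = 5%, against 69.1% if they are scored absent. The ratio is not diluted if the loss is non-informative.

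**The case against.** A reader might infer that every participant in care outside Nyanza is recorded as absent and that the primary contrast is therefore diluted. The documents do not support that.

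- **Recorded status.** The protocol nowhere says such a person counts as absent. All lost participants are traced and transfer is its own category. The end-of-study survey asks whether the person is in care and where. Status can be known without a site visit, so a verdict of not retained under Hypothesis 4 does not follow either.
- **Direction.** Dilution needs similar shares in both arms. The second unequal case above leaves the risk ratio at 0.50.
- **Size.** Planned permanent movers are excluded (for the next six months in the exclusion criteria, 12 months on the locator form), and the pilot ascertained 98.6% of outcomes. Both suggest few cases. A first missed appointment after about day 275 (365 − 90) cannot become a 90-day absence within 12 months, so the model above overstates the effect. At 175 to 180 per arm, power stays above 80% at x = 1.4%.
- **Supporting text.** The Measurements wording "any other clinics from which he or she receives HIV care during the course of the study" describes sources of covariates, so it is weak evidence about outcome collection. Scoring missing viral loads as non-suppressed under Hypothesis 5 is a separate, explicit choice with its own sensitivity analysis.
- **Place of the rule.** A censoring rule for transfers can properly sit in a statistical analysis plan, which is not shown here.

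All of this stands. It does not remove the conflict over which histories are collected. That is a protocol matter, and an analysis plan can only work with what was collected. Knowing that a transfer happened also does not supply the next visit date that Hypothesis 2 needs.

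**Conclusion.** The contradiction in scope is real and bears on both primary outcomes. If the Nyanza limit is followed, participants in care outside the province have no post-transfer visits on file, and their care may be scored as time out of care or as absence. Whether it is so scored is not fixed by the text.

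The size and direction are unknown. Under the assumption of equal shares, with every such participant becoming an event, the loss at 156 per arm is about 3 percentage points of power at x = 1.4%, 7 at 3% and 11 at 5%. With the full 175 to 180 per arm and no other attrition, power falls below 80% at 3% and 5% but not at 1.4%. Unequal shares could move the estimate either way, so validity is at stake as well as power.

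**What to change.** Remove the Nyanza limit from both sentences in the Study Design Overview, so that it agrees with Measurements and Appendix F. Outside the province, accept telephone confirmation of visit dates from the receiving clinic, or OpenMRS data, which Measurements already allows, instead of a site visit.

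Where a transfer is confirmed but the history cannot be obtained, end follow-up for Hypotheses 1 and 2 at the transfer date rather than scoring absence. This rule may sit in the protocol or the analysis plan, but it should be fixed before outcome data are seen.

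The cost is a change of wording and a few telephone calls. Out-of-province data will be somewhat less complete than chart review, the documents do not say how far OpenMRS reaches beyond the study clinics, and a few participants will be censored.
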